## 4.5.2 Study Implementation

### 4.5.2.1 Visit 1 (Screening Period: –1 week to 0 week)

#### (1) Basic Information

Obtain informed consent; record demographic data, medical history, allergy history, adverse events, and concomitant medications/treatments.

#### (2) Laboratory Tests

- Complete blood count and C-reactive protein, including hemoglobin, hematocrit, red blood cell count, white blood cell count, platelet count, and C-reactive protein;
- Blood biochemistry, including AST, ALT, total bilirubin, direct bilirubin, albumin, total protein, serum creatinine, LDL cholesterol, potassium, and sodium;
- NT-proBNP;
- Urinalysis: leukocytes, erythrocytes, and ketone bodies;
- Stool tests: fecal occult blood and transferrin.

#### (3) Imaging Examinations

- Echocardiography, including atrial and ventricular diameters, ventricular wall thickness, LVEF, and valvular regurgitation;
- CMR, including LVEDVi, left ventricular end-systolic volume, left ventricular stroke volume, left ventricular cardiac output, left ventricular mass, LVEF, right ventricular end-diastolic diameter, right ventricular end-diastolic volume, right ventricular end-systolic volume, right ventricular stroke volume, right ventricular cardiac output, left atrial diameter, LAVi, right atrial diameter, delayed enhancement, extracellular volume, and global longitudinal strain;

#### (4) Other Assessments

Other evaluations include 24-hour Holter ECG and KCCQ score.

##### **4.5.2.2 Visit2 (Baseline/Randomization 0 Week)**

Investigators will enroll participants who have passed screening and meet the inclusion and exclusion criteria.

After enrollment, participants will be randomized in a 1:1 ratio using a random number table into either the experimental group or the control group. The experimental group will undergo stepwise withdrawal of HF medications, while the control group will continue standard HF therapy.

##### **4.5.2.3 Visit 3-7 (Monthly Follow-up)**

Participants will monitor blood pressure and heart rate daily. Monthly assessments will include NT-proBNP, liver and renal function tests with electrolytes, urinalysis, echocardiography, and 24-hour Holter ECG. At 6 months, CMR will be repeated along with KCCQ questionnaire evaluation. Echocardiography and 24-hour Holter ECG will also be performed, and current medication use will be recorded monthly.

##### **4.5.2.4 Visit 8 (6-Month Post-Randomization)**

Participants will continue daily monitoring of blood pressure and heart rate. Monthly assessments will include the aforementioned laboratory tests, echocardiography, and 24-hour Holter ECG, with current medication use recorded each month. At 6 months, CMR will be repeated, and the KCCQ questionnaire will be administered.

#### **4.6 Imaging Assessment Methods**

##### **4.6.1 Echocardiography Protocol**

Echocardiography was performed by experienced operators from the same echocardiography team using a commercially available system (Epic 7c, Philips Healthcare, Best, The Netherlands) equipped with a 3.5 MHz transducer for 2-dimensional imaging. All measurements were conducted in accordance with current guideline recommendations. LVEDD and left ventricular end-systolic diameters were manually traced at end-diastole and end-systole in both apical 4- and 2-chamber views. LVEF was calculated using the modified Simpson's biplane method. LA diameter was measured using the biplane method from apical views. Diastolic function was evaluated by measuring the mitral inflow E/A ratio and deceleration time of mitral inflow. In addition, tissue Doppler imaging was performed in the apical 4-chamber view. Peak systolic (S'), early diastolic (E') velocities of the medial and lateral mitral annulus, and the corresponding E/E' ratio were calculated. Sector width and

imaging depth were optimized individually to ensure the highest achievable frame rate and the optimal visualization.

#### **4.6.2 Cardiac Magnetic Resonance Scan Protocol**

CMR scans were performed on a 3-Tesla MR scanner (Ingenia CX, Philips Healthcare, Best, The Netherlands) with a 32-channel phased-array coil and a retrospective ECG gating. The CMR protocol comprised a standardized protocol including balanced steady-state free precession sequences for left ventricle cine images (short axis, 2, 3, 4 chambers), and Modified Look-locker inversion recovery (MOLLI) sequences for both pre- and post-contrast T1 mapping images, and late gadolinium enhancement images (LGE). LGE imaging was implemented 10 min after intravenous administration of contrast medium (0.2 mmol/kg; Magnevist gadopentetate dimeglumine, Bayer Healthcare, Bayer, Berlin, Germany) using a phase-sensitive inversion-recovery (PSIR) TFE sequence. General CMR analyses (cardiac function, myocardial strain, extent and distribution of LGE, T1 mapping) were conducted using the CVI 42 software (Circle Cardiovascular Imaging, Calgary, Canada) by a radiologist who was blinded to treatment allocation.

#### **4.7 Bias Control**

##### **4.7.1 Prospective Trial**

The prospective design of this trial, with a pre-specified study population and standardized protocol, inherently mitigates biases common in retrospective studies, such as recall and selection bias. The analysis will follow a modified intention-to-treat (ITT) principle, including all randomized participants who are not lost to follow-up in their originally assigned groups, thereby minimizing attrition bias. This approach helps ensure the robustness and credibility of the trial's findings.

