|-----------------------------|----------------------------------------------------------------------------------------------------------------------------------------------------------------------------------------------------------------------------------------------------------------------------------------------------------------------------------------------------------------------------------------------------------------------------------------------------------------------------------------------|
|                             | 
 
3) NT-proBNP;
 
4) KCCQ-12 score;
 
5) Heart rate;
 
6) Systolic blood pressure;
 
7) Diastolic blood pressure.
 
 
 
3. Recurrence of atrial tachyarrhythmia and atrial tachyarrhythmia burden;
 
4. Adverse drug events, including symptomatic hypotension, renal dysfunction, hyperkalemia, bradycardia, diabetic ketoacidosis and urogenital infection.
 
 |
| Statistical Analysis | The study will follow a modified intention-to-treat approach. All patients, with the exception of those lost to follow-up, will be included in the statistical analysis according to their original randomization assignment.                                                                                                                                                                                                                                                                |

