##### **(2) Withdrawal Initiated by the Participant**

a) The participant, for any reason, is unwilling or unable to continue the clinical trial and requests termination of participation;

b) The participant does not explicitly request withdrawal but discontinues treatment and follow-up, resulting in loss to follow-up.

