##### **(3) Handling of Withdrawn Cases**

For all withdrawn cases, the status of clinical trial completion and the reasons for withdrawal should be documented. After a participant withdraws, the investigator should make every effort to contact the participant, inquire about the reason for withdrawal, record the most recent clinical symptoms, and complete any assessments that can still be performed. If withdrawal is due to an adverse event, the investigator should provide appropriate medical management based on the participant's condition.

When a participant or their legal guardian requests withdrawal from the trial, the investigator should ask whether previously collected data may still be used for the clinical study, and the response should be documented in the raw records.

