### **4.3 Study Outcomes**

#### **4.3.1 Primary Endpoint**

HF deterioration within 6 months.

Defined as meeting any of the following criteria:

(1) A decrease in LVEF on echocardiography by >10% in absolute value and to <55%;

- (2) An increase in LVEDD on echocardiography by >10% and exceeding the normal range;
- (3) A twofold rise in NT-proBNP and to >400 ng/L;
- (4) None of the above criteria are met, but worsening HF signs and/or symptoms are present,, as adjudicated by the research team.

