## **5.2 Principles of Statistical Analysis**

Statistical analysis will be performed according to the modified intention-to-treat (ITT) approach.

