## **5.4 Handling of Missing and Aberrant Data**

A statistical analysis plan will be developed before the trial begins. After database lock, statistical analyses will be conducted according to the plan, and a statistical analysis report will be generated based on the results.

**5.4.1 Handling of Missing Data:** Missing data will not be imputed; analyses will be performed using the available data.

**5.4.2 Handling of Erroneous Data:** During data management, quality control will be performed on the database. Identified erroneous data will be queried to the investigators via a data query form. Corrections will be made based on the investigators' written responses. The database will only be locked after all erroneous data have been corrected.

**5.4.3 Handling of Implausible Data:** During data management, logical checks will be performed on the database. Implausible data will be queried to the investigators via a data query form. Adjustments will be made based on the investigators' written responses. The database will only be locked after all implausible data have been resolved.

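### The modified ITT set leaves out randomised patients lost to follow-up and is said to minimise attrition bias; that exclusion can create the bias, and no exception is stated for events recorded before loss

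*Protocol*

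**What the plan says.** The analysis set is described twice, in the same way. The Statistical Analysis row of the Protocol Summary reads: "All patients, with the exception of those lost to follow-up, will be included in the statistical analysis according to their original randomization assignment". Section 4.7.1, under Bias Control, describes the set as "including all randomized participants who are not lost to follow-up in their originally assigned groups, thereby minimizing attrition bias". Section 5.2 names the approach without defining it: "Statistical analysis will be performed according to the modified intention-to-treat (ITT) approach".

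Four other places bear on the rule:

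- **What loss is.** Section 4.2.3.1 (2) describes it: "The participant does not explicitly request withdrawal but discontinues treatment and follow-up, resulting in loss to follow-up". It sets no minimum follow-up time and makes no exception for a patient who already has an event.
- **What is collected from patients who leave.** Section 4.2.3.1 (3) asks the investigator to "record the most recent clinical symptoms, and complete any assessments that can still be performed".
- **Missing data.** Section 5.4.1: "Missing data will not be imputed; analyses will be performed using the available data".
- **Endpoint and visits.** The primary endpoint in section 4.3.1 is "HF deterioration within 6 months", met by any one of four criteria. Section 4.5.2.3 schedules the measurements behind them: "Monthly assessments will include NT-proBNP, liver and renal function tests with electrolytes, urinalysis, echocardiography, and 24-hour Holter ECG".

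The primary comparison is a chi-squared or Fisher's exact test, two-sided, at P ≤ 0.05 (section 5.3.2), with 25 patients planned per group.

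**The concern.** Attrition bias arises when patients lost after randomisation are left out of the comparison and their loss is related to arm or outcome. Section 4.7.1 presents that omission as the remedy. Keeping patients in their assigned groups deals with crossover between strategies. It does nothing about patients who are missing from the analysis.

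The second problem is what happens to data already in hand. Because the endpoint is any deterioration within 6 months and is assessed monthly, a patient who meets a criterion at month 2 and is lost at month 4 has a known primary outcome. Read literally, the set definition removes that patient from both numerator and denominator. There is no missing-data reason to do so.

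At stake is the primary safety comparison of an open-label trial in which a patient's experience of the assigned strategy could influence whether he or she stays. With 25 per arm, a few exclusions can move the estimate noticeably.

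**Working it through.** **No plan figure to reproduce.** The protocol gives no event rates, loss rate, power or margin, so every event count and loss rate below is an assumption. Only the 25 per arm and the two-sided Fisher test at 0.05 come from the protocol.

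**Step 1: the texts side by side.** The Summary and section 4.7.1 exclude lost patients with no exception. Section 5.2 adds nothing. Section 5.4.1 says available data are used, and section 4.2.3.1 (3) gathers last symptoms and remaining assessments from patients who leave. Neither of these returns a lost patient to the analysis set, and both sit badly with a rule that would discard such data. The passages need reconciling.

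**Step 2: effect of dropping patients with an event before loss.** If *a* of 25 withdrawal patients and *b* of 25 control patients have an event, and *k* withdrawal patients with an event are excluded as lost, the difference moves from a/25 − b/25 to (a − k)/(25 − k) − b/25.

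| Assumed events | k | Analysed | Difference (points) | Fisher p |
|---|---|---|---|---|
| 7 v 1 | 0 | 7/25 v 1/25 | 28.0 − 4.0 = 24.0 | 0.049 |
| 7 v 1 | 1 | 6/24 v 1/25 | 25.0 − 4.0 = 21.0 | 0.049 |
| 7 v 1 | 2 | 5/23 v 1/25 | 21.7 − 4.0 = 17.7 | 0.091 |
| 6 v 0 | 0 | 6/25 v 0/25 | 24.0 | 0.022 |
| 6 v 0 | 2 | 4/23 v 0/25 | 17.4 | 0.046 |
| 6 v 0 | 3 | 3/22 v 0/25 | 13.6 | 0.095 |

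Two or three exclusions can carry the result across the protocol's threshold.

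**Step 3: the direction is not fixed.** From 7/25 v 1/25, dropping two event-free withdrawal patients gives 7/23 − 1/25 = 30.4 − 4.0 = 26.4 points. Dropping the one control patient with an event gives 7/25 − 0/24 = 28.0 points. Both move away from 24.0 in the opposite direction to Step 2.

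**Step 4: bias in one arm's risk.** With true risk p, and loss probabilities q1 in patients with an event and q0 in patients without:

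observed risk = p(1 − q1) / [p(1 − q1) + (1 − p)(1 − q0)]

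For p = 0.30:

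- q1 = q0 = 0.10: 0.27/0.90 = 30.0%, no bias.
- q1 = 0.20, q0 = 0.05: 0.240/0.905 = 26.5%.
- q1 = 0.30, q0 = 0.05: 0.210/0.875 = 24.0%.
- q1 = 0.40, q0 = 0.05: 0.180/0.845 = 21.3%.

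The bias comes from loss that is related to outcome, which the exclusion does nothing to prevent.

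**The case against.** **No sentence says that a patient with a recorded event is removed.** That is so. A reader might infer that the protocol deliberately discards documented events. It does not say this; it states a rule without an exception, and section 5.4.1 on available data could be read the other way. What stands is that the set definition, taken literally, excludes such patients, and that nothing in the protocol settles the conflict.

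**The bias need not favour withdrawal.** A reader might infer that harm will be hidden, because patients who feel worse after withdrawal may leave. The documents give no loss rates and no reasons for loss by arm. Patients who feel well, or control patients with adverse drug effects, could leave too, and Step 3 shows the estimate moving the other way. The direction is open.

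**The size is easily overstated.** A reader might take each dropped patient to be worth 1/25 = 4 points. From 5/25 (20.0%), dropping one event patient gives 4/24 = 16.7%, a change of 3.3 points. Dropping one event-free patient gives 5/24 = 20.8%, a change of 0.8 points. Nor does every scenario change the test's conclusion: 5/25 v 1/25 (p = 0.19) reduced to 2/22 v 1/25 (p = 0.59) is non-significant throughout.

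**This is a small pilot with close follow-up.** Sections 4.1 and 5.1 present it as a feasibility step towards a larger trial, at one centre, over 6 months with monthly visits, so losses may be few. That lowers the severity. It does not make the statement in section 4.7.1 true.

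**The statistical analysis plan may add detail.** Section 5.4 promises one, and it is not at hand. The absence of a sensitivity analysis from the protocol is therefore not a fault in itself. The exclusion rule and its rationale, however, are in the protocol.

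**Conclusion.** Wrong as written. Excluding randomised patients lost to follow-up does not minimise attrition bias; where loss is related to arm or outcome, it creates that bias. The lack of an exception for events recorded before loss conflicts with the available-data rule and with the data collection required for patients who leave.

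Under the assumed counts, dropping two withdrawal-arm patients with earlier events lowers the risk difference by 24.0 − 17.7 = 6.3 points in one case and 24.0 − 17.4 = 6.6 points in the other, and in the first it moves Fisher p from 0.049 to 0.091. These sizes rest on loss being concentrated among withdrawal-arm patients with events and on the literal reading of the rule. With no losses the set equals full intention-to-treat and nothing changes; with loss unrelated to outcome within each arm, Step 4 shows no bias in the risk. Severity: should be fixed, given the pilot design.

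**What to change.** - In the Protocol Summary and section 4.7.1, define the primary analysis set as all randomised patients in their assigned arm. Section 5.2 holds no definition of its own, so the approach it names should simply follow the new one.
- State that every primary event recorded before loss counts.
- Delete the closing clause on attrition bias in section 4.7.1.
- Report a bounding sensitivity analysis for patients lost without a recorded event: lost withdrawal patients counted as events and lost control patients as event-free, then the reverse. For example, if 5 of 25 withdrawal patients and 1 of 25 controls have recorded events and two event-free withdrawal patients are lost, the bounds are 7/25 − 1/25 = 24.0 points and 5/25 − 1/25 = 16.0 points.

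The chi-squared or Fisher comparison can stay. A Kaplan-Meier 6-month risk difference is an optional supplement. Its censoring assumes non-informative loss, so it does not answer the case of a patient who worsens and leaves before an event is recorded; the bounding analysis does.

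Cost: protocol wording and modest programming. Monthly assessments are already scheduled, so no new visits or patients are needed.

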##### **4.7.2 Investigator Training**

Before the initiation of the clinical trial, monitors will provide training to investigators on the study protocol, ensuring that they understand and are familiar with the medication regimen and follow-up procedures.

##### **4.7.3. Standardized Implementation of Inclusion and Exclusion Criteria**

Participants will be screened according to the trial's inclusion and exclusion criteria to minimize selection bias.

## **5. Statistical Methods**

### **5.1 Sample Size Calculation**

This study is designed to explore the feasibility of a future large-scale trial. The sample size is set at 50 participants, based on a 2019 Lancet study investigating withdrawal of HF medications in patients with dilated cardiomyopathy.

## **5.2 Principles of Statistical Analysis**

Statistical analysis will be performed according to the modified intention-to-treat (ITT) approach.

## **5.3 Methods of Statistical Analysis**

### **5.3.1 Statistical Analysis Software**

R version 4.2.1 or higher will be used for all analyses.

### **5.3.2 General Principles**

**Descriptive Statistics:** For quantitative variables, the number of observations, mean, standard deviation, median, interquartile range, minimum, and maximum will be reported. For categorical variables, counts and percentages for each category will be presented.

**Inferential Statistics:** Unless otherwise specified, all statistical tests will be two-sided, and a P-value  $\leq 0.05$  (two-sided) will be considered statistically significant. The primary endpoint was compared using the chi-squared or Fisher's exact test. Secondary endpoints were compared using Wilcoxon rank-sum test for continuous variables, and chi-squared or Fisher's exact test for categorical variables.

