## **4. Study Design**

### **4.1 Overall Design**

This trial is a single-center, open-label, pilot, randomized controlled trial designed to assess the feasibility of conducting a large-scale investigation. The study will enroll patients with AF and HF who demonstrate improvement in cardiac function after catheter ablation.

Patients who sign an ethics committee–approved informed consent form and are deemed eligible for enrollment by the investigators may be included in the study. After enrollment, participants will be randomized 1:1 to phased GDMT withdrawal or continuation using computer-generated sequences via SAS software. The physicians responsible for enrollment and assignment of participants were blinded to the random allocation sequence. The experimental group will undergo stepwise withdrawal of GDMT, while the control group

will continue GDMT. All participants will be followed for 6 months to compare the safety and efficacy outcomes between the two groups.

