#### **4.3.2 Secondary Endpoints**

- (1) Composite of cardiovascular death, hospitalization for HF, non-fatal stroke, or non-fatal myocardial infarction;
- (2) Changes from baseline to 6 months in the following parameters:
  - a) Echocardiography: LVEF, LVEDD;
  - b) Cardiac magnetic resonance (CMR): LVEF, left ventricular end-diastolic volume index (LVEDVi), left ventricular global longitudinal strain (LV-GLS), and percentage of late gadolinium enhancement (LGE);
  - c) NT-proBNP;
  - d) KCCQ-12 score;
  - e) Heart rate;
  - f) Systolic blood pressure;
  - g) Diastolic blood pressure.
- (3) Recurrence of atrial tachyarrhythmia and atrial tachyarrhythmia burden;
- (4) Adverse drug events, including symptomatic hypotension, renal dysfunction, hyperkalemia, bradycardia, diabetic ketoacidosis and urogenital infection.

Definitions: 1) renal dysfunction: a decrease in the eGFR of  $\geq 50\%$  or a decrease of  $>30$  mL/min/1.73 m^2 from randomization to  $<60$  mL/min/1.73 m^2; 2) hyperkalemia: serum potassium  $>5.5$  mmol/L; and 3) bradycardia: heart rate at rest  $<40$  beats/min.

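### Section 5.3.2 gives all 20 secondary comparisons of a feasibility pilot the same 0.05 significance label as the primary endpoint, with roughly a one-in-four to one-in-two chance of at least one false positive

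*Protocol*

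**What the plan says.** Protocol section 5.3.2 opens its inferential paragraph with "Unless otherwise specified" and then states that "all statistical tests will be two-sided". A P value at or below 0.05 "two-sided) will be considered statistically significant". The paragraph goes on to name the tests. The primary endpoint is compared by chi-squared or Fisher's exact test. For the rest, "Secondary endpoints were compared using Wilcoxon rank-sum test for continuous variables", and "chi-squared or Fisher's exact test for categorical variables". The significance rule therefore covers primary and secondary endpoints alike.

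Section 4.3.2 lists the secondary endpoints. They begin with "Composite of cardiovascular death, hospitalization for HF, non-fatal stroke, or non-fatal myocardial infarction" and continue with "Changes from baseline to 6 months in the following parameters", covering echocardiography, CMR, NT-proBNP, KCCQ-12, heart rate and blood pressure. Atrial tachyarrhythmia recurrence and burden follow, then six named adverse drug events.

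On purpose, section 4.1 calls the trial a pilot "designed to assess the feasibility of conducting a large-scale investigation". Section 5.1 repeats the feasibility aim and sets 50 patients by analogy with an earlier withdrawal trial in dilated cardiomyopathy. Section 5.4 says that a statistical analysis plan will be written before the trial begins. That plan is not available here.

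**The concern.** The rule is written down, so this is not a detail that the protocol leaves open. As it stands, any of the secondary comparisons that reaches 0.05 may be reported with the same label as the primary endpoint. No order of importance and no exploratory status qualifies it.

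That fits poorly with a study whose stated aim is to find out whether a larger trial is feasible. A chance difference in, say, CMR strain or KCCQ-12, in either direction, could be presented as a finding about withdrawal of heart failure drugs and carried into the thinking behind the larger trial. The label also says little about the adverse drug events. At 25 per arm, sparse events can rarely reach 0.05, so their absence from the list of significant results would mean little.

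**Working it through.** The protocol states no familywise error rate, effect size or power, so there is no figure of its own to reproduce.

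**Inputs from the protocol**
- Per-test threshold: P ≤ 0.05, two-sided (section 5.3.2).
- Arms: 25 and 25 (Protocol Summary, sample size).
- Tests: Wilcoxon rank-sum for continuous outcomes; chi-squared or Fisher's exact for categorical outcomes (section 5.3.2).
- Continuous comparisons (section 4.3.2): 2 echocardiographic + 4 CMR + NT-proBNP + KCCQ-12 + heart rate + systolic pressure + diastolic pressure + arrhythmia burden = 12.
- Binary comparisons (section 4.3.2): composite + recurrence + 6 adverse drug events = 8.
- Total: 12 + 8 = 20. This takes the six adverse drug events one by one. Pooled into one, they would leave 15 comparisons, still led by the 12 continuous ones.

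**Assumptions (the protocol gives no values)**
- Base event rates: composite 2%, recurrence 20%, each adverse drug event 4%. Higher case: 4%, 30% and 10%.
- Equal pairwise correlation between endpoints, 0 to 0.7.
- Chi-squared where the smallest expected count is at least 5, otherwise Fisher.
- Global null: withdrawal changes none of the secondary outcomes, unless stated otherwise.

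**Step 1: textbook ceiling.** For k independent tests of exact size 5%, the chance of at least one false positive is 1 − 0.95^k.
- k = 20: 1 − 0.95^20 = 64.2%.
- k = 12 (continuous only): 1 − 0.95^12 = 46.0%.

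**Step 2: true size of the binary tests.** With 25 per arm, Fisher's test rejects a true null in 0.001% of trials at a 2% event rate, 0.03% at 4%, 0.9% at 10% and 2.2% at 20%. With no events in one arm, 5 in the other gives P = 0.0502 and 6 gives P = 0.022, so 6 versus 0 is the smallest such split that counts. The eight binary tests therefore add little.

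**Step 3: expected number of false positives at base rates.** Continuous: 12 × 0.05 = 0.6. Binary, by Fisher: 0.00001 + 0.022 + 6 × 0.0003 ≈ 0.02. The total is about 0.6.

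**Step 4: simulation of the mixed set** (6,000 runs per case; Monte Carlo standard error about √(0.45 × 0.55/6000) = 0.6 percentage points). Chance of at least one P ≤ 0.05:

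| Case | Corr. 0 | 0.3 | 0.5 | 0.7 |
|---|---|---|---|---|
| 12 Wilcoxon + 8 binary, base rates | 45% | 42% | 34% | 26% |
| Same, higher event rates | 49% | 45% | 36% | not run |
| 9 Wilcoxon + 8 binary, base rates (heart rate and both pressures truly differ) | 39% | 34% | 29% | not run |
| 20 tests of full 5% size (reference) | 64% | 54% | 42% | 29% |

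The first entry, 45%, lies just below the 46.0% of Step 1 because the Wilcoxon test was run with a continuity correction, which makes it slightly conservative (43% for the 12 continuous tests alone).

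Under the global null and with the protocol's own tests, the range is roughly 25% to 49%. That is about 5 to 10 times the 5% of a single test.

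**The case against.** The strongest reply is that the rule in section 5.3.2 is only a default. Its opening words allow exceptions, section 5.4 promises a statistical analysis plan, and exploratory labelling and multiplicity handling commonly belong there. The protocol already separates primary from secondary endpoints and calls itself a pilot, and no decision about the larger trial is tied to a secondary P value. One may add that a pilot sized by analogy can barely confirm its primary endpoint either.

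Much of this stands. The lack of a multiplicity adjustment in the protocol is no error, the analysis plan may already hold the needed sentence, and influence on the larger trial is a possibility, not something the protocol provides for. What does not fall away is that section 5.3.2 positively assigns the label to all tests, and no exception appears anywhere in the protocol. As for the primary endpoint, it is a single named comparison, so keeping the label there does not multiply the error.

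A reader might also infer more than the text supports:
- *A false secondary finding is more likely than not.* That needs something close to 20 independent tests of full 5% size. No scenario run with the protocol's own tests exceeds 49%.
- *One false positive should be expected.* That is 20 × 0.05; at the low event rates assumed here the figure is about 0.6.
- *The small sample inflates the error.* It does not. For the sparse binary outcomes it lowers it.
- *Any significant secondary result would be false.* Sections 4.4.1 and 4.4.3 describe withdrawal of beta-blockers and ARNi/RASi and provide for raised blood pressure and rapid ventricular rate, so differences in heart rate and pressure may be real.
- *The protocol declares the secondary endpoints confirmatory.* It never does. It only gives them the same significance label.

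**Conclusion.** The point holds as one about labelling. Section 5.3.2 fixes a blanket 0.05 significance label for 20 secondary comparisons in a feasibility pilot, and nothing in the protocol marks them as exploratory. The resulting chance of at least one false significant secondary result is substantial but below one half. If heart rate and both blood pressures truly differ, it is 29% to 39% for correlations from 0.5 down to 0. These figures rest on assumed event rates, an equal-correlation model and no true effect on the outcomes counted as null. Severity is minor to moderate: the primary analysis is untouched, and the matter concerns what the pilot may claim from its secondary results.

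**What to change.** Amend section 5.3.2 so that the significance label applies to the primary endpoint only. State that secondary endpoints are exploratory and will be reported with between-group estimates, 95% confidence intervals and at most nominal P values, with no claim of significance. Align the statistical analysis plan; if it already says this, only the protocol sentence needs changing. Do not add a formal correction: Bonferroni over 20 tests would put the threshold at 0.05/20 = 0.0025 and further reduce sensitivity to harm signals that already rarely reach 0.05.

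The cost is one sentence, with no extra patients, visits or tests. The downside is that no individual secondary endpoint can be claimed as statistically significant.
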